## Abstract

**Background:**

Acupuncture has been widely applied in the clinic to treat irritable bowel syndrome (IBS), but the underlying mechanism remains unknown. Diffuse noxious inhibitory control (DNIC) is deficient in patients with IBS, which attenuates the systemic analgesic effect elicited by noxious stimulation that is remote from pain areas. Therefore, the aim of this study is to investigate the analgesic effect of electroacupuncture (EA) at homotopic or heterotopic acupoints on abdominal pain in patients with IBS.

**Methods/design:**

This study is a randomized, single-blinded, controlled, four-arm parallel trial. A total of 144 patients will be randomly assigned to four groups: a homotopic noxious stimulation group (group A), a homotopic innocuous stimulation group (group B), a heterotopic noxious stimulation group (group C), and a heterotopic innocuous stimulation group (group D). Each patient will receive 14 sessions of treatment, twice per week for 7 weeks. The primary outcome will be pain intensity measured with the visual analog scale. The secondary outcomes will include the IBS Symptom Severity Scale, IBS Quality of Life questionnaire, pain threshold (PT), and the Symptom Checklist-90 for psychological distress. The PT will be measured before and after every treatment. All other outcomes will be evaluated before the 1st treatment, after 7th and 14th treatment, and 3 months later during follow-up.

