## Methods/design

### Study design

This study is a single-blind randomized controlled trial (RCT) that aims to compare the analgesic effect of two homotopic acupoint groups (noxious intensity and innocuous intensity) and two heterotopic acupoint groups (noxious intensity and innocuous intensity) for IBS. A total of 144 female patients will be recruited from the Guangdong Provincial Hospital of Traditional Chinese Medicine. Patients will be randomized to the homotopic noxious stimulation group (group A), the homotopic innocuous stimulation group (group B), the heterotopic noxious stimulation group (group C), or the heterotopic innocuous stimulation group (group D) in a 1:1:1:1 ratio. Patients will receive 14 sessions of EA treatment twice a week for 7 weeks. Each session will last 30 min. The flowchart of the trial is shown in Fig. 1. The study schedule is detailed in Fig. 2. The Standard Protocol Items: Recommendations for Interventional Trials (SPIRIT) checklist is provided as Additional file 1.

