**Fig. 2 Fig2:**
[figure not shown]
Study schedule (SPIRIT figure). The schedule of enrollment, allocation, interventions, and assessments. *W4*: the 7th treatment during the 4th week, *W7*: the 14th treatment during the 7th week

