##### 2.6.2.2. Pain threshold (PT)

PT is a secondary outcome in this study, and is a more objective measure of pain than the VAS. The PT will be tested by a digital algometer (EP601C, East China Normal University of Science and Technology, Guangxi, China) immediately before and after each treatment. The most obviously tender point (Ashi point) on the abdomen will be tested. The patient will lie in a supine position on the treatment couch. The algometer has a 1-cm^2^ rubber probe, which will be pressed vertically against the abdominal wall. The trained assessor will position the algometer perpendicular to the tender point and apply gradual pressure at a steady rate of approximately 0.5 kg/cm^2^/s. The patient will request the treatment to be stopped when the applied pressure becomes painful, and the value on the digital algometer will be recorded. The pressure pain threshold will be measured three times at each point, with the average value collected for analysis.

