### Follow-up

All participants will be asked to return in 3 months for follow-up. The researcher will contact participants via telephone to collect therapeutic effect information after the treatment has been completed for 3 months.

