### 2.11. Statistical analyses

The statistical analyses will be performed by a statistician who will be blinded to the treatments and study protocol. All data will be analyzed according to intention-to-treat (ITT) principles to reduce deviation. Non-continuous variables will be analyzed by chi-square test. All normally distributed continuous variables will be described by mean ± standard error (SEM). The paired *t* test will be used to compare the outcome measurements before and after treatment. The differences between group and time will be analyzed by repeated measures analysis of variance (ANOVA). If we find a significant overall difference among the four groups for a particular outcome, we will use the post hoc test (Newman-Keuls test) to adjust for multiple comparisons to determine the statistical differences among pairwise groups. All analyses will be conducted with SPSS (version 21.0) software. A *P* value of 0.05 or less will be considered statistically significant.

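### The VAS and questionnaires are timed by session count and the 3-month contact by treatment completion, so a patient who stops early has no defined end-of-treatment assessment, although ITT is claimed

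*Protocol article*

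**What the plan says.** All references are to the protocol article.

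- **Abstract, Methods/design.** For everything except pain threshold (PT): "All other outcomes will be evaluated before the 1st treatment, after 7th and 14th treatment, and 3 months later during follow-up". For PT: "The PT will be measured before and after every treatment".
- **Study design.** "Patients will receive 14 sessions of EA treatment twice a week for 7 weeks".
- **Fig. 2 caption.** The label W4 stands for "the 7th treatment during the 4th week" and W7 for "the 14th treatment during the 7th week".
- **Follow-up.** The first sentence asks every participant back at three months. The second says the researcher will telephone to "collect therapeutic effect information after the treatment has been completed for 3 months".
- **Pain threshold (2.6.2.2).** PT is taken "immediately before and after each treatment".
- **Sample size (2.8).** 144 patients, 36 per group, with an allowance of 20% for attrition.
- **Statistical analyses (2.11).** "All data will be analyzed according to intention-to-treat (ITT) principles to reduce deviation". Groups and times are compared by repeated measures ANOVA.

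**The concern.** An ITT comparison needs outcomes from randomised patients whether or not they finish treatment. Here the trigger for the primary outcome and the questionnaires is the receipt of a given session, and the start of the 3-month clock is the completion of treatment. A patient who stops has no session 14, so the article gives her no date for the end-of-treatment VAS. Stopping treatment and losing that outcome then tend to coincide. How missing values are handled can be settled in an analysis plan, but a plan cannot supply a VAS score that no visit collected.

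This matters more here than in many trials because the arms differ in a feature that could affect tolerance. Groups A and C receive current 30% above the patient's pain threshold and groups B and D 30% below it, in both cases for 14 sessions of 30 minutes. The choice between the two intensities is a stated aim. If more patients stop in A and C, the end-of-treatment intensity contrast would be made among those who tolerated the assigned stimulation.

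**Working it through.** **1. The stated schedule.** Two sessions a week for 7 weeks is 2 × 7 = 14 sessions. Session 7 falls in week 4 (7/2 = 3.5, rounded up) and session 14 in week 7 (14/2 = 7). For a patient who attends every session on time, the session counts and the W4/W7 labels therefore agree. They part only when a session is missed or treatment stops, and the article does not say which anchor then governs.

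**2. What is defined for whom (VAS, IBS-SSS, IBS-QOL, SCL-90).**

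| Last session received | Mid-treatment | End of treatment | 3 months |
|---|---|---|---|
| 0 to 6 | none defined | none defined | invited, date unclear |
| 7 to 13 | done | none defined | invited, date unclear |
| 14 | done | done | defined |

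PT is separate. It is taken at every session, so anyone who has had one session has a post-treatment PT value, and the series ends with her last session.

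If the last session among stoppers were uniform over 0 to 13 (an assumption), 7/14 = 50% would have the mid-treatment assessment and 13/14 = 93% would have at least one post-treatment PT value.

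**3. How many patients.** Group sizes are consistent: 4 × 36 = 144. At 20% attrition, 0.20 × 36 = 7.2 per arm and 0.20 × 144 = 28.8 overall. This is the most that can be affected within the allowance when it is spread evenly. It is reached only if all attrition is stopping before session 14. Patients lost to contact or withdrawing consent would be missing under any schedule.

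**4. Possible distortion of the intensity contrast.** Let *p* be the proportion stopping in an arm and *g* the amount by which stoppers fare worse than completers. The completers' mean exceeds the full-arm mean by *p* × *g*. With the same *g* in all arms,

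shift in contrast = (*p* noxious − *p* innocuous) × *g*.

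The article gives neither stopping rates by arm nor *g*, so every input below is an assumption.

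- In mm: a 10-point difference in stopping and a 10 mm gap give 0.10 × 10 = 1 mm. A 20-point difference and a 20 mm gap give 0.20 × 20 = 4 mm. The shift favours the noxious arms.
- In SD units, with *g* from 0.25 to 1.0: 20% v 20% gives 0. 25% v 15% gives 0.025 to 0.10. 30% v 10% gives 0.05 to 0.20.

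**5. Which contrast.** The homotopic side is A and B, and the heterotopic side is C and D. Each has one noxious and one innocuous arm, so stopping driven only by intensity, with the same *g*, cancels there. The issue bears on A and C against B and D.

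**6. Timing drift.** If a missed session were made up in the next slot (the article states no such rule) and each slot were missed independently with probability 2%, 5% or 10%, the share reaching session 14 after week 7 would be 1 − 0.98^14 = 25%, 1 − 0.95^14 = 51% or 1 − 0.90^14 = 77%. This only illustrates that the two anchors can separate, and the VAS rates the preceding week.

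**The case against.** A reader might infer that every post-baseline outcome is lost once a patient stops, and that the ITT analysis is therefore already a completers' analysis. The document does not support that.

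- PT is measured at each session, so a patient with any treatment has post-treatment data. One who stops after session 7 also has the mid-treatment VAS.
- The Follow-up section asks all participants back, without restriction to completers. The natural reading includes early stoppers at three months, even though the next sentence leaves their date unclear.
- The W4 and W7 labels give calendar weeks. The grid of Fig. 2 was not available for this review and could carry visit rules.
- Nothing says that assessments end when treatment stops. A journal article commonly leaves continued assessment, visit windows and missing-data handling to the full protocol or analysis plan, so their absence here is no fault.
- Mid-treatment VAS, 3-month data and PT can inform missing end-of-treatment values under stated assumptions.

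These points stand, and they limit the finding. They do not remove it. W4 and W7 are themselves defined by treatments, so the labels give a stopper no date. The invitation to all participants covers the 3-month contact, not the end of treatment. The point concerns a trigger that the article does state, not a detail that it omits. Repeated measures ANOVA in its classical form needs complete data, so a patient with a mid-treatment but no end-of-treatment value could drop out of it too. The article does not say which form will be used, so that remains a risk.

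**Conclusion.** The point holds as a conflict between the stated assessment trigger and the ITT claim, confined to the VAS and questionnaires. The end-of-treatment assessment is undefined for anyone stopping before session 14, the mid-treatment one for anyone stopping before session 7, and the 3-month date is unclear for both. It is worth correcting, but it does not demonstrate that ITT has failed.

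The number affected is at most about 7 of 36 per arm (about 29 of 144), assuming that attrition matches the 20% allowance, is evenly spread and is entirely early stopping. The effect on the intensity contrast cannot be sized from the document. The 1 to 4 mm range rests wholly on assumed stopping rates and an assumed stopper-completer gap. It is zero if stopping is equal and stoppers differ from completers alike across arms. The homotopic-versus-heterotopic hypothesis is not threatened by stopping that depends on intensity alone.

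**What to change.** - Time the VAS, IBS-SSS, IBS-QOL and SCL-90 from randomisation (or session 1): end of week 4, end of week 7, and three months after the scheduled end of week 7, each with a window.
- Apply these dates to every randomised patient, whatever the number of sessions received.
- State that stopping EA does not end outcome collection.
- Record the number of sessions received and the date and reason for stopping.
- Bring the Abstract, the Fig. 2 labels and the Follow-up section into line with this.

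The cost is a wording change and a few case report form fields. The downside is a few additional contacts with patients who have stopped, which can use the telephone contact already planned. No extra patients are needed. If the full protocol already has these rules, aligning the published wording is enough.

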**Discussion:**

The aim of this study is to assess the analgesic effect of EA at homotopic (abdomen) acupoints and heterotopic (lower limb) acupoints on abdominal pain in patients with IBS, as well as the difference in analgesic effects between noxious and innocuous stimulation.

**Trial registration:**

Chinese Clinical Trial Registry, ChiCTR-IPR-15006879. Registered on 5 August 2015.

**Electronic supplementary material:**

The online version of this article (10.1186/s13063-018-2948-1) contains supplementary material, which is available to authorized users.

## Background

Irritable bowel syndrome (IBS) is a common functional gastrointestinal disease characterized by recurring symptoms of abdominal pain or discomfort, bloating, and altered bowel function in the absence of structural, inflammatory, or biochemical abnormalities [1]. It is reported that the prevalence of IBS varies from 7 to 21% worldwide [2]. The prevalence of IBS is higher in females than in males and is higher in patients younger than 50 years [3]. Among affected patients, abdominal pain is the most bothersome symptom and has the largest impact on quality of life [4, 5]. Since the pathogenesis of abdominal pain is still incompletely understood, the treatment is a challenging clinical problem [6, 7]. Many patients turn to complementary and alternative medicines, such as acupuncture [8].

Acupuncture has been clinically applied to treat acute and chronic pain for more than two millennia. Electroacupuncture (EA) is a modern adaptation of traditional Chinese acupuncture therapy. By adding direct current to the needles, the stimulation of acupoints can be amplified, which improves the therapeutic effect. EA is being increasingly used for pain relief for IBS. One clinical trial showed that EA is effective in lowering the severity and frequency of abdominal pain and increasing quality of life, compared with sham acupuncture [9]. Another previous trial suggested that EA may have positive effects on modulating pain sensations by altering the activation of neural pathways [10]. Animal experiments showed that EA attenuated visceral hyperalgesia through down-regulation of central serotonergic activities in the brain-gut axis [11]. The acupoint is the basis of acupuncture. The specific function of an acupoint is determined by the anatomical relationship between the disease focus and the segmental location of the acupoint [12]. Generally, acupoints may be classified as heterotopic or homotopic points, in terms of spinal segmental innervation patterns [13]. The pain-modulating effect of heterotopic and homotopic points involves different neuronal mechanisms. Innocuous stimulation applied to the pain area mainly excites large fibers (Aβ-fibers), exerting segmental inhibition through the spinal cord [14]. In contrast, noxious stimulation applied outside of the pain area activates small-diameter fibers (Aδ- and/or C-fibers), which produce extrasegmental analgesia through diffuse noxious inhibitory control (DNIC) [15].

Under normal circumstances, pain can be reduced by a conditioning noxious stimulus anywhere in the body; this is the definition of DNIC [16]. DNIC efficiency indicates the function of the endogenous pain modulation system for an individual patient [17]. DNIC function is critical for chronic pain prediction and treatment in clinical practice. However, deficient DNIC mechanisms have been found in various chronic pain conditions, including IBS [18], fibromyalgia [19], and temporomandibular joint disorder [18]. Impaired DNIC in patients with IBS was detected by King et al. by sensitivity to prolonged heat pain and the efficacy of pain inhibition. Compared with healthy controls, patients with IBS show increased pain sensitivity and reduced endogenous pain inhibition [18]. The selection of acupoints is an important consideration for clinical effects. Commonly, a combination of homotopic and heterotopic points has been used in IBS trials [9–11]. However, the difference between the effects of homotopic and heterotopic point stimulation is unknown.

Therefore, the aim of this study is to assess the analgesic effect of EA stimulation at homotopic (abdomen) and heterotopic (lower limbs) acupoints on abdominal pain in patients with IBS. Furthermore, we aim to determine which type of current intensity (noxious or innocuous) is the optimal stimulation for IBS clinical applications.

## Methods/design

### Study design

This study is a single-blind randomized controlled trial (RCT) that aims to compare the analgesic effect of two homotopic acupoint groups (noxious intensity and innocuous intensity) and two heterotopic acupoint groups (noxious intensity and innocuous intensity) for IBS. A total of 144 female patients will be recruited from the Guangdong Provincial Hospital of Traditional Chinese Medicine. Patients will be randomized to the homotopic noxious stimulation group (group A), the homotopic innocuous stimulation group (group B), the heterotopic noxious stimulation group (group C), or the heterotopic innocuous stimulation group (group D) in a 1:1:1:1 ratio. Patients will receive 14 sessions of EA treatment twice a week for 7 weeks. Each session will last 30 min. The flowchart of the trial is shown in Fig. 1. The study schedule is detailed in Fig. 2. The Standard Protocol Items: Recommendations for Interventional Trials (SPIRIT) checklist is provided as Additional file 1.

**Fig. 1 Fig1:**
[figure not shown]
Flowchart of the study design. We will randomize 144 participants to the four groups. The interventions will last 30 min and will be carried out twice a week for 7 weeks. The study period will consist of the baseline, 7 weeks of treatment, and 3 months follow-up

**Fig. 2 Fig2:**
[figure not shown]
Study schedule (SPIRIT figure). The schedule of enrollment, allocation, interventions, and assessments. *W4*: the 7th treatment during the 4th week, *W7*: the 14th treatment during the 7th week

### Participants

#### Inclusion criteria

Patients who meet the following criteria are eligible for inclusion in the study: (1) they are females aged between 18 and 50 years, (2) they meet the criteria for IBS according to the Rome III diagnostic criteria, (3) IBS has been their main complaint for at least 6 months, (4) their average abdominal pain score has been greater than 30 mm (on a scale of 0–100 mm, with 0 indicating no pain and 100 the worst imaginable pain) in the past 2 weeks, and (5) they have signed an informed consent form.

#### Exclusion criteria

Patients will be excluded if they: (1) have a history of previous abdominal surgery related to IBS symptoms (other than appendectomy), (2) are currently taking antidepressant agents including tricyclic antidepressants and selective serotonin reuptake inhibitors, (3) have a history of usage of anticholinergic, antipsychotic, or antispasmodic drugs during the last 2 weeks, (4) are currently participating in another trial or have enrolled in a trial during the past month, (5) are currently pregnant or planning to become pregnant, (6) have a Hamilton Depression Rating Scale (HAMD) count of 21 points or more, (7) have a serious concomitant disease of the heart, liver, or kidney, or have diabetes, (8) have a blood system disease such as thrombocytopenia with bleeding tendency.

#### Recruitment

All participants will be recruited through advertisements on notice boards in the Traditional Chinese Medicine Hospital of Guangdong Province. If a patient is interested in participating she will contact the researcher by WeChat or telephone. Then the patient will be screened based on the inclusion and exclusion criteria in a face-to-face interview with the researcher. The researcher is expected to explain the study in detail, including the potential benefits and risks. Once a participant agrees to join the RCT, she will be asked to sign an informed consent form before randomization.

### Randomization

We plan to use the random block method. A designated researcher who has no contact with any participant will conduct the randomization. The random number table is generated by the “completely random design” program of the Package for the Encyclopedia of Medical Statistics for Windows (PEMS 3.1, West China School of Public Health, Sichuan, China). All participants will be assigned to four groups with a 1:1:1:1 allocation ratio. The random sequence will be generated in a block size of 4. The researcher then will make randomization assignment cards and put the cards into sequentially numbered, opaque envelopes. According to the time order in which participants pass the screening test, another researcher will arrange the patients into different groups and inform the acupuncturists of the group assignment.

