### Blinding

In this RCT procedure, the patients, data collection staff, and data analysts will be blinded. However, the acupuncturist knows the treatment allocation due to the nature of the acupuncture manipulation. During the intervention, the acupuncturist and the data collection researcher will be separated immediately after the treatment starts and are instructed not to exchange information. Data collection staff and data analysts have no information about grouping or treatment.

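### A single fixed block of 4 for four equal arms makes every fourth allocation deducible from the previous three, and the Randomization section describes list generation in two ways that conflict

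*Protocol article*

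**What the plan says.** All of the following is in the protocol article.

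- **Method (Randomization):** "We plan to use the random block method". The ratio is equal: "All participants will be assigned to four groups with a 1:1:1:1 allocation ratio". One block size is given: "The random sequence will be generated in a block size of 4".
- **Source of the list (Randomization):** "The random number table is generated by the “completely random design” program of the Package for the Encyclopedia of Medical Statistics for Windows".
- **Concealment (Randomization):** the list-maker has no contact with participants and is to "put the cards into sequentially numbered, opaque envelopes". A second researcher then places patients into groups in the order in which they pass screening, and tells the acupuncturist the group.
- **Who is unblinded (Blinding):** "the acupuncturist knows the treatment allocation due to the nature of the acupuncture manipulation". Under Interventions, one acupuncturist gives all treatments.
- **Screening (Recruitment):** a researcher screens face to face and obtains consent before randomization.
- **Size and setting (Sample size; Study design):** 144 patients, 36 per arm, from one hospital. No stratification is described.
- **Timing (Trial status):** recruitment is in progress.

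**The concern.** With four equal arms, 4 is the smallest block that can be used, and so the most predictable. Envelopes stop staff from reading the list ahead of time. They do not stop anyone from working out the next card from those already used. With one hospital and no strata described, there appears to be a single sequence to follow, and the block size is in print while patients are still being enrolled.

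At stake is selection bias. If someone who can foresee an allocation also influences who is entered or when, the arms can come to differ in prognosis. There is some room for discretion: entry depends partly on a self-rated average pain score above 30 mm, and the order of passing screening decides which card a patient gets. The Discussion also states an expectation that the homotopic arms will do better.

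Separately, a completely randomised design has no blocks, so a reader cannot tell from this section how the list was produced.

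**Working it through.** **Inputs:** 4 arms at 1:1:1:1 and block size 4 (Randomization); 144 patients, 36 per arm (Sample size).

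**1. The plan's own counts.** 144 / 4 = 36 complete blocks. One patient per arm per block gives 36 per arm. This agrees with the stated figure. It checks allocation counts only, since the article says that no formula was used for the sample size.

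**2. Allocations known with certainty.** A block of 4 with each arm once has 4! = 24 possible orders. Given the first three places, exactly one arm is left in all 24. One certain place per block × 36 blocks = 36 allocations, and 36 / 144 = 25%.

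**3. Best-guess accuracy over all places.** The chance of a correct guess is 1/4, 1/3, 1/2 and 1 at places one to four. The sum is 25/12 = 2.083 per block. Dividing by 4 gives 52.1%, and 36 × 2.083 = 75 correct of 144. Guessing by chance gives 144 / 4 = 36 correct (25%).

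**4. What mixed block sizes would change.** The first row is exact. The others are simulated (1,500 lists of 144). Assumptions: each size is equally likely, and the guesser knows all past allocations and the set of sizes, but not the size of the current block.

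| Block sizes | Certain in advance, of 144 | Correct best guesses, of 144 |
|---|---|---|
| 4 only (as planned) | 36 (25%) | 75 (52%) |
| 4 and 8 | 10.8 (7%) | 69.9 (49%) |
| 4, 8 and 12 | 5.1 (4%) | 66.5 (46%) |
| 8 and 12 | 6.6 (5%) | 64.8 (45%) |

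Mixing removes most of the certainty. It lowers overall guessing accuracy much less.

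**5. Who holds the knowledge.** The assigning researcher learns each allocation on assignment. The acupuncturist learns all of them, being the only person who treats. The Randomization section distinguishes the assigner from the list-maker, but nothing distinguishes the assigner from the screening researcher in the Recruitment section. No section gives the acupuncturist a part in screening or enrolment.

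**6. The two descriptions.** A block method with block size 4 and a program called "completely random design" stand in the same paragraph. Read as design terms they exclude each other. The program may, however, only supply random numbers that are then ordered within blocks. The article does not say.

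**The case against.** The strongest reply is that selection bias needs one person who both knows past allocations and influences enrolment, and the article does not show such a person. The acupuncturist is not said to screen. The list-maker is independent, the envelopes are opaque and numbered, consent comes before randomization, and assignment follows the order of passing screening. This stands as far as it goes: a reader might infer that allocation concealment fails, and the documents do not support that. They support only that allocations could be predicted by people who may or may not be separate from screening.

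A reader might also infer that the self-rated primary outcome makes the problem worse. Subjectivity bears mainly on how outcomes are assessed, and the Blinding section says that patients and data collectors are blinded. It adds nothing to the argument about who is entered.

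A third inference would be that the named program means unrestricted draws, and so arms well away from 36. That is not supported. A completely randomised design can fix 36 per arm by permuting 144 places, and the stated ratio, block size and group sizes all point away from independent draws. Nor can both problems apply at once: if the list has no blocks, the 25% of determined places disappears.

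Finally, mixed blocks lower correct guesses only from 75 to about 66 with sizes 4, 8 and 12, so keeping past allocations from the screener is the more direct protection. That also stands, and the fix includes it.

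**Conclusion.** The point holds in limited form. As written, the scheme determines 36 of 144 allocations (25%) from the previous three and allows 52% correct best guesses against 25% by chance. These figures assume that the list really is blocked in fours as one sequence, and that the guesser knows all past allocations and where each block starts. The stated safeguards do not prevent the deduction. Whether it could affect enrolment depends on whether the assigner or the acupuncturist also influences screening, which the article leaves open. Selection bias is a possible risk and its size cannot be computed.

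The two descriptions of list generation conflict and need reconciling. This is a fault of description, not evidence that the list is unblocked or the arms unequal.

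This is an avoidable weakness that is cheap to correct, and not a reason to doubt the comparison as such.

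**What to change.** 1. For allocations not yet made, prepare a new list in permuted blocks of randomly mixed sizes, all multiples of 4 (such as 4, 8 and 12). Only the list-maker should know the sizes. Start it at the end of a current block of 4.
2. State that the person who screens and enrols neither opens envelopes nor learns past allocations.
3. State how the existing list was actually generated: what the program produced, and whether and how its output was arranged in blocks of 4. Do not simply delete one description, because that would presume which is true and could misreport the method.

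**Cost:** a new set of envelopes and a short amendment. If enrolment stops inside a block of 12, which holds each arm 3 times, arms can differ by at most 3 patients.

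**Limit:** only remaining allocations are protected, and the article does not say how many there are. If *r* remain, about *r*/4 are determined under the present scheme, against about 0.035*r* with sizes 4, 8 and 12 (5.1 / 144 = 0.035). If half remain (*r* = 72, an assumption), that is 18 against about 2.5. If none remain, only items 2 and 3 are left, as matters to report.
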